# Data tabulation

All data is collected by entering the required fields into the eCRF (electronic case report form) built into the REDCap system. In principle, each visit should be entered within 7 days of the subject's visit to the hospital. Since there are no entry fields for personal information such as medical record numbers, a separate correspondence chart that identifies individuals should be prepared and kept strictly by the principal and subcontracting physicians.

# Statistics Analysis

## Data handling

When compiling data for observation and inspection items specified in the plan by time period, data for inspection items performed on days or at times outside the acceptable range shall be treated as missing. For missing values, LOCF completes the values when the main analysis is performed.

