# Study aims

Object disease patients: 80 female RA patients who met the 2010 ACR/EULAR classification criteria. Test food: Test tablets containing Brazilian propolis

Evaluation items：

・Anthropometry: height, weight, waist circumference

・Disease activity：DAS28-ESR・DAS28-CRP・SDAI・CDAI

・ADL：mHAQ

・Laboratory data: General items（WBC, RBC, Hb, Ht, Plt, AST, ALT, γ-GTP, T-Bil, Cre, BUN, CRP, ESR, RF, TP, Alb, T-chol, HDL-chol, TG, Na, Cl, K, Mg, P, Ca, FBS, special items（anti CCP antibody, MMP-3, IL-6, IL-17, IL-10）

・Blood pressure

・Lifestyle survey: smoking status, alcohol consumption, exercise habits, sleep time, supplement use and type

・QOL:SF－36

・Objective arthritis assessment: sonographic examination of joints

　Eighty female RA patients with moderate disease activity by DAS28-ESR will be divided into two groups: 40 patients treated with Brazilian propolis (P group) and 40 patients treated with placebo balls (C group). In doing so, allocation will be by double-blind randomization using a stratified replacement block method, with facilities in strata. The test food is manufactured at Yamada Bee Company, Inc., Ltd. for 40 people in each group, plus 5 people in the reserve group, for a 3-month supply of 5 tablets per day x (84 days + 7 days in reserve) x 45 people = 2,0475 tablets. This is one set and we plan to make two sets for 6 months. The P group will take 5 tablets of the test diet containing Brazilian propolis (508.5 mg as P) per day, and the C group will take 5 tablets of the placebo diet without Brazilian propolis per day. In both groups, DAS28-ESR will be compared at 0, 12, 24, and 36 weeks, and the above evaluation items will also be compared.

The purpose of this study is to clarify whether Brazilian propolis has an suppressive effect on disease activity not only in mouse RA models but also in RA patients.

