　Subcontractor name: LSI Medience Co.Ltd.

・QOL：SF－36

　　・ADL：mHAQ

・Disease activity：DAS28-ESR・DAS28-CRP・SDAI・CDAI

・Sonographic examination of joints：sonographic examination of synovitis in 7 joints on the side with stronger symptom at baseline (unchanged during the observation period) (2nd and 3rd metacarpophalangeal (MP) joints, 2nd and 3rd proximal interphalangeal (PIP) joints, wrist, and 2nd and 5th metatarsophalangeal (MTP) joints) using both grayscale (GS) (grade 0–3) and power-Doppler (PD) scale (grade 0–3)

Timetable

| Item | pre-  observation | Start administering the test foods | Administration period | End of test food administration | post-  observation |
| --- | --- | --- | --- | --- | --- |
| Period | Before  1-4 weeks | 0 week | After 12 weeks  (±7day) | After 24 weeks  (±7day) | After 12 weeks |
| Medical Examination | 1 | 2 | 3 | 4 | 5 |
| Consent obtain | ○ |  |  |  |  |
| Check patient background | ○ |  |  |  |  |
| Test food administration |  |  |  |  |  |
| Subjective symptoms and other findings | ○ | ○ | ● | ● | ● |
| Observation of adverse events^a^ |  |  | ● | ● | ● |
| Anthropometry^b^ |  | ○ |  | ● |  |
| Blood pressure and pulse measurement |  | ○ | ● | ● | ● |
| Hematological examination |  | ○ | ● | ● | ● |
| Blood Biochemistry Test |  | ○ | ● | ● | ● |
| Sonographic examination of joints |  | ○ | ● | ● | ● |
| QOL assessment |  | ○ |  | ● |  |
| Disease activity assessment^c^ | ○ | ○ | ● | ● | ● |

　Items marked with an asterisk ○ are items to be performed before administration of the test food, and items marked with an ● are items to be performed after administration of the test food.

a: Adverse events are all events that are undesirable, such as side effects, regardless of whether they are causally related to the test food.

b: Measure height, weight, and abdominal circumference as anthropometry.

c: Evaluate DAS28-ESR, DAS28-CRP, SDAI, and CDAI for disease activity.

Blood tests should be performed under fasting conditions to rule out the effects of diet.

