# Discontinuation criteria for individual subjects

　　The principal investigator or sub-investigator will discontinue the study for subjects who are unable to continue the study due to the following reasons, and will take appropriate treatment based on the benefit to the subject. In addition, scheduled surveys/inspections shall be conducted as soon as possible to make a decision (Except in cases where it cannot be conducted due to withdrawal of consent, etc.). If consent is withdrawn after the administration of the study food has begun, it should be made as clear as possible whether the withdrawal is due to ineffectiveness of the study food or an adverse event, or whether it is due to an accidental event (e.g., change of location), and it should be recorded so that it can be used as a reference for the selection of the case for efficacy and safety evaluation. The investigator or sub-investigator should record the date of discontinuation, reason for discontinuation, and comments in the case report form. After discontinuation of the study, if any of the following items 4)-6), 10) are found, hematological and biochemical tests should be performed to confirm safety. In addition, medical examinations will be conducted as deemed necessary by the physician for each symptom. Patients will be followed up for one year after treatment as deemed necessary by the physician according to the examination results. In particular, if the study is discontinued due to the occurrence of an adverse event, follow-up will be conducted until the patient recovers to the original state as much as possible.

1. When the subject declines to participate in the study or withdraws consent
2. Other reasons depending on the subject (e.g., too busy, hospital transfer, relocation)
3. If it is found that the eligibility is not satisfied after registration
4. When it is judged inadvisable to continue administration of the test food due to worsening of the primary disease.
5. If it is difficult to continue the study due to exacerbation of complications
6. If it is difficult to continue the study due to adverse events
7. When pregnancy is detected
8. If the entire study is discontinued
9. If the physician deems it appropriate to stop the study for any other reason.

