# Evaluation items

## Primary endpoints

　The primary endpoint of this study is the change in disease activity DAS28-ESR at 24 weeks after the start of the test food intake.

【Evidence of setting】

　In this study, we will investigate the suppressive effect of Brazilian propolis on the disease activity of RA. The above item of disease activity is the gold standard not only for ACR/EULAR but also for the assessment of disease activity in RA worldwide.

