## Efficacy analysis

The analysis population will be defined as the largest analysis set (full analysis set; FAS), defined as subjects assigned to the study who have consumed the study food at least once and have had at least one efficacy assessment after administration of the study food. Supplemental analyses will also be performed with a per protocol set (PPS) that conforms to the protocol. Hypothesis testing will be two-tailed at the 5% significance level, with two-tailed 95% confidence intervals.

A significance test for the coefficients of the groups will be conducted using a model in which the DAS28-ESR at the end of the intervention for the primary endpoint is the objective variable, the group (control or intervention) is the explanatory variable, and the value of the DAS28-ESR at week 0 is the covariate. In order to confirm the robustness of the results associated with the completion of missing values by LOCF, a mixed-effects model will be used as a supplementary analysis for the primary endpoint. In this case, the normality of the DAS28-ESR at the end of the intervention is checked by histogram, and if normality is not found, the variable is transformed by log transformation or other methods to follow a normal distribution before being used in the analysis. As a secondary analysis, when the objective variable is DAS28-ESR, the interaction between group (control, intervention) and time point (12 weeks, 24 weeks) and between group and time point will be used as explanatory variables, and the analysis will be conducted using a mixed-effects model with the value of DAS28-ESR at week 0 as the covariate and subjects as the variable effect, and the correlation structure of time points will be unstructured.

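### DAS28-ESR values measured outside the ±7-day window are discarded and replaced by LOCF in the primary analysis, and nothing exempts the assessment at discontinuation

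*Protocol*

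**What the plan says.** Protocol section 14.1 (Data handling) contains two linked rules. First, "data for inspection items performed on days or at times outside the acceptable range shall be treated as missing". Second, "For missing values, LOCF completes the values when the main analysis is performed".

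The acceptable range is not defined in that section. The timetable in section 8 gives ±7 days at week 12 and the same at week 24 ("After 24 weeks (±7day"), and no other window.

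These rules act on the primary endpoint. Section 12.1 states: "The primary endpoint of this study is the change in disease activity DAS28-ESR at 24 weeks after the start of the test food intake". In the primary model of section 14.2, "DAS28-ESR at the end of the intervention for the primary endpoint is the objective variable", with the week-0 value as covariate.

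Section 14.2 also plans a supplementary analysis: "In order to confirm the robustness of the results associated with the completion of missing values by LOCF, a mixed-effects model will be used".

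For patients who stop, section 9 asks that "scheduled surveys/inspections shall be conducted as soon as possible to make a decision". Worsening of the primary disease is one of the listed reasons for stopping. Section 9 does not say how the result enters the efficacy analysis.

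**The concern.** The rule throws away primary-endpoint data that were actually collected and puts an older measurement in their place. A value taken 8 days from the target date is closer to what the endpoint describes than a value taken around week 12. A timing rule meant to protect the endpoint therefore moves the analysed value much further from week 24.

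The same rule may reach the assessments made when a patient stops early. If those are set to missing because they fall between visit windows, LOCF goes back to the last accepted scheduled visit. For a patient who stopped because of worsening, that value can predate the worsening.

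At stake are the precision of the primary comparison and, if replacement is unequal between arms, its bias. Section 15.2 leaves little slack: it needs 39 per group, plans 40, and expects few dropouts.

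**Working it through.** **1. Which values are replaced, and by what.** Week 12 is day 84, so its window is days 77–91. Week 24 is day 168, so its window is days 161–175.

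| Week-24 visit held on | Distance from day 168 | Status under 14.1 | Value used instead | Age gap to the discarded value |
| --- | --- | --- | --- | --- |
| day 176 | 8 days late | missing | week 12 (days 77–91) | 176 − 91 = 85 to 176 − 77 = 99 days |
| day 160 | 8 days early | missing | week 12 (days 77–91) | 160 − 91 = 69 to 160 − 77 = 83 days |

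The substitute lies 168 − 91 = 77 to 168 − 77 = 91 days from the target; the discarded value lies 8 days from it. If week 12 is also missing or out of window, the week-0 value is carried.

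**2. Does the supplementary model recover the values?** The mixed model in section 14.2 is there to check the LOCF step. It avoids carrying week 12 forward, but section 14.1 has already set the out-of-window value to missing and no text restores it for that model.

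**3. Discontinuation assessments.** Section 9 ties them to the moment of stopping, not to a visit. They will usually fall outside both windows. Section 14.1 neither exempts them nor assigns them to a visit. Two readings are open: (a) literal, the value is out of range, is set to missing, and week 12 or week 0 is carried; (b) the value is outside the scope of the window rule and is itself the last observation carried forward. The protocol does not choose between them.

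**4. The plan's own sample size.** Inputs from section 15.2: δ = 0.5, σ = 0.78, α = 0.05 (two-sided, section 14.2), power 80%, two-sample t-test. The normal approximation gives n = 2 × [(1.960 + 0.842) × 0.78 / 0.5]² = 38.2, rounded up to 39 per group, as stated. The exact t-test gives 39.19; its power is 79.8% with 39 and 80.8% with 40 per group.

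**5. Illustration of size.** Two inputs are not in the protocol and are assumed: m, the share of week-24 values replaced (equal in both arms), and f, the fraction of the 0.5 effect already present in the carried value. The SD is held at 0.78. The expected difference is 0.5 × [1 − m(1 − f)]; power is from the exact t-test at 40 per group.

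| f | m = 10%: difference, power | m = 20%: difference, power |
| --- | --- | --- |
| 1 (full effect at week 12) | 0.50, 80.8% | 0.50, 80.8% |
| 0.8 | 0.49, 79.2% | 0.48, 77.6% |
| 0.5 | 0.475, 76.7% | 0.45, 72.2% |
| 0 (baseline carried) | 0.45, 72.2% | 0.40, 62.0% |

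The row f = 0.8 corresponds to 0.4/0.5, where 0.4 is the 12-week difference that section 15.2 quotes from a dietary intervention study. Using it for propolis is also an assumption.

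**The case against.** The late edge of the window has a rationale. Each 12-week kit holds 91 daily sachets ("5 tablets per day x (84 days + 7 days in reserve) x 45 people" is the production figure). A reader might infer that two kits cover 182 days, so that a day-176 visit is still on treatment. The documents do not support that in general. Leftovers are returned at each visit (sections 7.4, 7.8 and 8) and the second supply is handed over at week 12 (section 7.7). After an on-time day-84 visit, supply ends at about 84 + 91 = day 175, the last day of the window; day 182 requires a week-12 visit that was itself 7 days late. This stands: values well after day 175 are mostly off test food, and some late bound is reasonable. It does not justify discarding early visits, or replacing a value a day past supply with one from week 12.

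Deletion of discontinuation assessments is one reading, not stated content. An analyst could carry that value forward, and the mapping of early-termination visits is often left to an SAP, which is not at hand. This also stands, so the point here is an unresolved conflict between sections 9 and 14.1.

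The share of out-of-window visits may be small: section 5.2 excludes patients who cannot attend regularly, and section 18.2 says visit frequency matches normal care. No figure is given either way.

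Finally, the planned mixed model offers partial protection. It removes the carry-forward, but not the loss of the measured value.

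**Conclusion.** The point holds for scheduled visits. Sections 8, 14.1 and 14.2 together fix a rule under which a DAS28-ESR measured 8 or more days from week 24 is dropped and, in the primary analysis, replaced by one normally about 12 weeks older. This is a rule the protocol states, not a detail left for later, and the loss is avoidable because the values exist.

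For discontinuation assessments the finding is narrower: the literal text discards them, nothing exempts or maps them, and the protocol should settle which reading applies.

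A reader might infer that the treatment effect is necessarily diluted. The documents do not support that. With equal replacement in both arms there is no loss if the full effect is present at week 12, and if replacement differs between arms the bias can go either way. Nor do they support a specific loss of power. The range given, from no loss to 72.2% at f = 0.5 and 20% replaced (62.0% if baseline is carried), rests on assumed m and f, an unchanged SD, and a t-test in place of the planned baseline-adjusted model.

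**What to change.** Amend section 14.1 as follows.

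- In the FAS primary analysis, use the measured DAS28-ESR nearest to week 24 within a wider analysis window fixed before unblinding. Bound that window on the late side with regard to the end of test-food intake. Alternatively, use actual assessment time in the mixed model.
- State that an assessment made at discontinuation counts as an observed value at its actual time and is never replaced by an older one.
- Keep ±7 days as the target for visit conduct and as a criterion for the PPS or a sensitivity analysis.

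The window should not simply be split at the midpoints between visits. That would take in weeks 18 to 30, and week 30 is day 210, about five weeks after supply ends for a patient with an on-time week-12 visit.

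The cost is a few sentences, with no new data, visits or sample size. The downside is somewhat more spread in measurement timing and a few values taken shortly before or after the end of intake.

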## Secondary analysis

Analyses of secondary endpoints will be conducted to provide supplementary insights to the primary analyses of the study. The secondary endpoints will be analyzed with exploratory intent and will not be adjusted for multiplicity. 1) DAS28-CRP, SDAI, CDAI, at 12, 24, and 36 weeks after intake 2) QOL at 24 weeks after intake (SF-36), 3) ADL at 12, 24, and 36 weeks after intake: mHAQ 4) sonographic examination of joints (scale change) at 12, 24, and 36 weeks after the start of intake will be analyzed in the same way as the primary endpoint. A frequency table will be prepared for each administration group regarding the occurrence of adverse events. In the case of serious adverse events, Kaplan-Meier curves will be generated for survival analysis until the occurrence of the event, and the groups will be compared using Cox proportional hazards model with DAS28-ESR at 0 week as a covariate. For quantitative data on clinical laboratories, summary statistics will be calculated for each time point and the amount of change from before the start of the test food administration for each dose group, and a scatter plot will be created. For other qualitative data, a frequency table should be created for each administration group.

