## Interim analysis

The food to be administered is a health food that is already sold worldwide and is unlikely to cause serious adverse events. In addition, it is not a powerful drug, so it is unlikely that the effect will appear in a short period of time. Since the total administration study period is 24 weeks, we believe that there is little merit in conducting an interim analysis and will not conduct an interim analysis.

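### The primary week-24 test runs on LOCF-filled DAS28-ESR, while the mixed model already specified for weeks 12 and 24 is only supplementary; the two should change places

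*Protocol*

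**What the plan says.** The primary endpoint (Protocol 12.1) is the "change in disease activity DAS28-ESR at 24 weeks after the start of the test food intake". Section 14.2 fixes the test: DAS28-ESR when intake ends is the response, group is the explanatory variable and week-0 DAS28-ESR is the covariate. It is fitted in a full analysis set of subjects with at least one intake and at least one later efficacy assessment.

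Two rules in section 14.1 decide which values enter that test. First, "data for inspection items performed on days or at times outside the acceptable range shall be treated as missing"; the timetable in section 8 allows 7 days either side of weeks 12 and 24. Second, "For missing values, LOCF completes the values when the main analysis is performed".

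Section 14.2 adds that "a mixed-effects model will be used as a supplementary analysis for the primary endpoint", as a check on LOCF. It then describes, as a secondary analysis, a mixed model with group, time point (weeks 12 and 24), their interaction and week-0 DAS28-ESR, and with "subjects as the variable effect, and the correlation structure of time points will be unstructured". Section 14.3 says that the secondary efficacy endpoints "will be analyzed in the same way as the primary endpoint".

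Section 15.2 gives no missing rate and says only that few dropouts are expected.

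**The concern.** Week 12 is the only scheduled assessment between baseline and week 24, so LOCF mostly scores a missing week-24 result as if disease activity had stood still for the second half of treatment. A week-24 visit outside the window meets the same fate: the measured value is set aside and an older one is used. The filled value then counts as observed, so its uncertainty is not carried into the standard error.

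Two things can go wrong. If the effect is still building after week 12, the estimate is pulled towards zero. If patients leave because they are worse (section 9 lists worsening of RA as a ground for stopping) and do so more often in one arm, carrying forward their high week-12 scores shifts the comparison towards the arm with fewer losses, even with no true effect.

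The plan already contains a model that handles both cases under missing at random, but it does not supply the headline estimate and p-value. If the two analyses disagree, the LOCF result is the primary one.

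**Working it through.** **Inputs from Protocol 14.2 and 15.2.** Effect 0.5, SD 0.78, two-sided alpha 0.05, power 80%, 39 required and 40 planned per group.

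**Inputs assumed.** The missing rate, the share of the effect present at week 12, the correlation between weeks 12 and 24, and how strongly loss depends on the week-12 score. The protocol gives none of these.

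**Step 1: the plan's own figure.** n per group = 2 × [0.78 × (1.960 + 0.842) / 0.5]² = 38.2, rounded up to 39. It reproduces. By the noncentral t the requirement is 39.2, and power is 79.8% at 39 and 80.8% at 40 per group. There is little slack.

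**Step 2: random loss, equal in both arms.** With a fraction d missing at week 24 and effect Δ12 at week 12, the expected LOCF difference is (1 − d) × 0.5 + d × Δ12. Example, d = 0.20 and Δ12 = 0.25: 0.80 × 0.5 + 0.20 × 0.25 = 0.450. Power is for a t-test with 40 per arm and SD 0.78.

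| Missing | Half the effect at week 12: difference (power) | No effect at week 12: difference (power) |
|---|---|---|
| 5% | 0.4875 (78.8%) | 0.475 (76.7%) |
| 10% | 0.475 (76.7%) | 0.450 (72.2%) |
| 15% | 0.4625 (74.5%) | 0.425 (67.2%) |
| 20% | 0.450 (72.2%) | 0.400 (62.0%) |

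At 30% with half the effect at week 12: 0.70 × 0.5 + 0.30 × 0.25 = 0.425; simulation gives 0.42 to 0.43. With the full effect at week 12 the difference stays at 0.500 for every d.

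**Step 3: loss that depends on the week-12 score.** Simulation with 40 per arm, SD 0.78, correlation 0.6 and 4,000 runs per scenario. The log-odds of loss rise by 0.7 per SD of week-12 score. For simplicity the baseline covariate is left out. Loss rates are nominal; P is propolis and C is placebo.

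| True week-24 effect; effect at week 12; loss P / C | LOCF difference (rejection rate) | Mixed-model difference (rejection rate) |
|---|---|---|
| -0.50; half; 15% / 15% | -0.472 (73.0%) | -0.501 (76.4%) |
| -0.50; none; 15% / 15% | -0.418 (59.2%) | -0.505 (75.6%) |
| -0.50; full; 15% / 15% | -0.512 (80.8%) | -0.500 (76.4%) |
| 0; none; 5% / 15% | -0.026 (5.4%) | 0.004 (5.4%) |
| 0; none; 15% / 5% | 0.027 (5.4%) | -0.001 (4.7%) |
| 0; none; 5% / 25% | -0.049 (5.8%) | 0.002 (5.2%) |

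The simulation error of a 5% rejection rate is √(0.05 × 0.95 / 4,000) = 0.3 percentage points, so the two 5.4% figures for LOCF do not differ clearly from 5%.

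**Step 4: sensitivity of the null result.** With 5% against 25% loss, other assumed correlations (such as 0.5 to 0.8) and selection strengths give a spurious difference of about 0.03 to 0.09 and type I error of about 5 to 8%. The upper end (0.085 and 7.7 to 8.1%) needs strong selection. At 5% against 10% the bias is 0.01 to 0.03 and type I error about 4 to 6%. With equal loss there is no systematic bias under the null.

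**Step 5: the covariance wording.** Over two time points an unstructured covariance has 3 parameters (two variances and one covariance). A separate random subject intercept makes 4 parameters for 3 estimable quantities. The marginal covariance is still identified, so the week-24 contrast does not change; the risk is a convergence warning.

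**The case against.** The strongest reply is that the protocol sees the risk: it plans a mixed model expressly to check the LOCF result. That stands. An alternative exists, and the fault is only its rank.

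Several stronger readings are tempting, and the text does not support them.

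- A reader might infer that the protocol contradicts its own LOCF rule, because section 14.4 says "it is unlikely that the effect will appear in a short period of time". That sentence explains why there is no interim analysis and does not call 12 weeks short. Section 15.2 points the other way: it cites a diet study with a 0.4-point DAS28-ESR difference at 12 weeks. How much effect is present at week 12 is unknown.
- A reader might take type I error near 8% as the expected result. It needs a fivefold difference in worsening-driven loss under no true effect, with strong selection, in a double-blind trial with coated tablets that expects few dropouts.
- A reader might say that only week 12 can ever be carried forward. Section 9 asks for the scheduled examinations as soon as possible at discontinuation, and LOCF might carry that value, including a recorded worsening. Whether the window rule discards it is not stated.
- A reader might state as fact that baseline SF-36 is carried to week 24 and week-24 values to week 36. Section 14.1 ties LOCF to the main analysis, and the phrase in section 14.3 may refer to the model only. Those endpoints are also exploratory.
- A reader might call the mixed model unfittable. The wording on subjects may simply name the repeated-measures unit and, as shown above, the contrast survives even a literal reading.

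The mixed model also has an assumption. If worsening after week 12 itself causes the loss, the data are not missing at random and that model is biased too.

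**Conclusion.** The point holds as a should-fix on the ranking of two planned analyses. The primary result rests on single imputation that assumes no change after the last value, although a model that avoids this assumption is already written into the same section.

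The size depends on quantities that the protocol does not give. At about 5% missing and half the effect at week 12, the loss is only about 0.01 points. At 15 to 20% with a late effect it becomes material, with power of 62 to 67% in the no-effect-at-week-12 case. The direction is not fixed: LOCF slightly overstates the effect when the full effect is present at week 12 and loss follows worsening, and it can err either way when loss is unequal. The documents do not support calling LOCF biased in every case, or claiming that the trial will have an inflated type I error.

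**What to change.** In Protocol sections 14.1 to 14.3:

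1. Make the mixed model for repeated measures the primary analysis: DAS28-ESR at weeks 12 and 24, with group, time, group-by-time interaction and week-0 DAS28-ESR, unstructured covariance, and the group contrast at week 24 as the primary test.
2. Move ANCOVA with LOCF to a sensitivity analysis, and say there whether the assessment made at discontinuation may be the value carried.
3. State that LOCF is not applied to SF-36, which the timetable schedules only at weeks 0 and 24, so that baseline would be carried forward. Exclude week 36 as well, where on-treatment values would be carried into the off-treatment period.
4. Say that subjects are the repeated-measures unit and that no separate random subject effect is added to the unstructured covariance.

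The change is to wording only. It needs no new data and no change to the planned 40 per group. The price is slightly wider intervals when data are missing, and the missing-at-random assumption should be stated.
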